### Outcome Measures

#### Stage 1 (Development Stage)

##### Demographic Characteristics

Participants will be asked both categorical (eg, gender, ethnicity, first language, and relationship to child) and continuous (eg, age) demographics. Demographic data on the patient population will also be collected. This will determine the profile of the families and health care professionals participating in the study.

##### Interview Topic Guide

The focus groups and interviews will follow a topic guide that aims to allow participants to review the current prototype of PUfP and provide feedback on all aspects of the prototype. Feedback will inform content and design while exploring the decision-making approaches of parents and clinicians. The topic guide will also explore parents’ emotions and how they impact the decision-making process. These interviews and focus groups are expected to provide preliminary qualitative input on the acceptability and usefulness of PUfP.

#### Stage 2 (Pilot-Testing Stage)

##### Participation Numbers

The number of sites that are approached and the number of sites agreeing to take part will be recorded, in addition to the number of participants agreeing to take part in the study. The proportion of participants completing various parts of the study (ie, consent, pretest, intervention, and posttest) will also be recorded. The app usage rates will also be collected using Google Analytics software.

##### The Control Preferences Scale for Pediatrics

The Control Preferences Scale for Pediatrics (CPS-P) [62] is an adaptation of the CPS [63]. This tool was originally developed to measure “the degree of control an individual wants to assume when decisions are being made about medical treatment” [64]. The CPS-P consists of 5 different scenarios describing different levels of control preference in decision making. The original scale has been tested in a variety of populations, ranging from the general public to highly stressed groups. The CPS has proven to be a clinically relevant, easily administered, valid, and reliable measure of preferred roles in health care decision making [64]. Permission was obtained to modify and reproduce the CPS-P. Therefore, we also adapted the questionnaire to obtain clinicians’ perspectives on how parents preferred to be involved in decisions. Clinicians will be asked to select 1 of 5 statements on whether “the parent leaves all mental health care and treatment decisions about the child to the practitioner” or “the parent shared responsibility for the mental health care and treatment decisions about the child with the practitioner.”

##### Pediatric Shared Decision-Making Questionnaire

The 9-item Pediatric Shared Decision-Making Questionnaire (PSDM-Q-9)—Parent (modified) version measures the extent to which parents are involved in the process of decision making from the perspective of the parent. The measure was developed for use in research and clinical practice. This tool is commonly used for the purposes of evaluation and quality improvement in health care. This measure is being applied in the case of preference-sensitive decisions—that is, when there are several options to be considered before a particular decision is made. This measure has shown face validity and high acceptance. Internal consistency yielded a Cronbach alpha of .938 in a test sample [65].

##### Spielberger State Anxiety Inventory Form for Adults

The Spielberger State Anxiety Inventory Form for Adults (STAI-AD) is a 40-item self-reported questionnaire commonly used as a measure of trait and state anxiety. It is used in research as an indicator of caregiver distress. The STAI-AD internal consistency coefficients ranged from .86 to .95; test-retest reliability coefficients ranged from .65 to .75 over a 2-month interval [66]. In addition, test-retest coefficients for this measure in another study are rated as highly significant with an intraclass correlation coefficient ranging from .39 to .89 [67].

##### Decisional Conflict Scale

The 16-item Decisional Conflict Scale was developed to elicit information concerning the decision maker’s (1) uncertainty in making a choice; (2) modifiable factors contributing to the uncertainty, such as lack of information, unclear values, and inadequate social support; and (3) perceived effective decision making [68]. This scale quantifies factors that contribute to uncertainty both during the process and at the outcome. Previous studies have shown that the psychometric properties of the scale are acceptable, and it is feasible and easy to administer [68].

##### Experience of Service Questionnaire

The Experience of Service Questionnaire (ESQ) measures service satisfaction and is widely used in CAMHS in the United Kingdom. The ESQ consists of 12 items and 3 free-text sections looking at what the respondents liked about the service, what they felt needed improving, and any other comments. The satisfaction with care construct will be obtained by adding up items 1 to 7, 11, and 12 [69]. These constructs are important to the study as the SDM process and outcome may impact parents’ perception of service satisfaction. On the basis of literature reviews of SDM [70], the research team agreed that the following questions also assess the key components of SDM: (1) I feel that the people who have seen my child listened to me; (2) It was easy to talk to the people who have seen my child; (4) My views and worries were taken seriously and (6) I have been given enough explanation about the help available here [40].

##### The Post-Study System Usability Questionnaire

The Post-Study Usability Questionnaire (PSSUQ) is a 19-item usability quantification survey developed in 1992 by the IBM Design Centre. The PSSUQ is generally used to quantify the usability of websites, apps, or any software or hardware that users interact with. The questionnaire is a series of statements describing the app that users agree or disagree with using a Likert scale [71]. For this study, the more general term *system* was replaced with the word *app*, and therefore, questions were more targeted, such as “I was able to complete the tasks and scenarios quickly using this app.” This measure aims to further assess the usability, appropriateness, acceptability, and feasibility of the overall intervention.

#### Planned Analysis

##### Stage 1: Development Stage

Data collected from focus groups and interviews will be analyzed using thematic analysis [72]. Themes will inform the development stage of the intervention by providing the relevant material to inform the content and design of the final version of PUfP. All interviews and focus group sessions will be audio-recorded digitally and transcribed. The computer package Atlas.ti or NVivo will be used to manage the data. Data will be coded using a combination of a priori themes and emergent themes [73].

##### Stage 2: Pilot-Testing Stage

The data collected will be analyzed with the main aim to reflect on potential improvements to the content of the intervention and informing the overall study design for a prospective RCT. The correlation between demographic data, app use, and outcome measures will be explored to identify target groups. Qualitative and quantitative evaluations will be carried out to examine the acceptability of the intervention as a useful decision aid for parents of children accessing CAMHS. In addition, between-group mean differences at the 2 time points (ie, baseline and follow-up) will be conducted. The standard deviations and intraclass correlation coefficients of the SDM measure will identify the parameters to enable planning for the subsequent trial. The outcome of these analyses will be used to calculate the sample size for the future RCT. Analyses will be conducted using the SPSS software and mostly presented descriptively. The main focus will be on descriptive data, with some exploratory significance testing. The amount of missing data will also be reported for each group.

Outcomes from stages 1 and 2 will be tested against a predetermined set of criteria. Multimedia Appendix 2 summarizes the criteria for assessing the feasibility of a prospective RCT upon completion of the feasibility trial.

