## Methods

### Design

This a 2-stage study involving a development stage (stage 1) where the intervention will be user-tested by clinicians and parents, and suggestions will be obtained for usage and upgrading of the prototype. The pilot-testing stage (stage 2) is a 3-arm, cluster randomized pilot trial with parents accessing CAMHS.

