#### Stage 2 (Pilot-Testing Stage)

The 18 sites identified will be randomly assigned to either control or 1 of the 2 intervention groups. Intervention group 1 (IG1) will receive the prospective version 1 of PUfP, which includes the *Support* and *Resources* features. Intervention group 2 (IG2) will receive version 2 of PUfP without these 2 features. The cluster randomization was completed independently of the research team, using R software guided by the balance algorithm [59]. Participant-level randomization will not be conducted for this study and parents at all selected sites will have a chance to participate in the study. The Standard Protocol Items: Recommendations for Interventional Trials (SPIRIT) diagram (see Table 1) and flow diagram (see Multimedia Appendix 1) illustrates the pathway through the trial, based on the trial protocol (version 1.3, November 14, 2018) approved by the NHS Research Ethics Committee and the Health Research Authority.

Stage 2 involves reinviting previous participants and obtaining informed consent from all the participants. Participants will be identified and recruited in identical ways as in the development stage. Participants will then be assigned to use the prototype and give feedback on usefulness, usability, and acceptability of the intervention. Up to 90 parents, and their respective clinicians, will be invited to participate in this stage with approximately 30 being allocated version 1 of PUfP, another 30 being allocated version 2, and the remaining 30 as the control group, receiving no app but subject to the same battery of questionnaires and treatment as usual. A sample ranging from 10 to 30 per arm should allow for calculations of feasibility and standardized effect sizes that are small to medium [60,61]. Power calculations, based on repeated measures, within – between comparisons among 3 groups for a single measure across two occasions, indicated that a total sample size of 30 would provide a power of 0.8 to detect an effect size of 0.3. Participants will be assigned to an intervention or control group based on the site from which they have been recruited to avoid contamination.

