## Results

Recruitment began in January 2019 and is scheduled to last for 10 months. Interviews and baseline data collection are currently in progress, and to date, 11 CAMH sites have been recruited to take part in the study. It is anticipated that data collection will be completed by October 2019.

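### Stage 2 randomises sites, but its one named between-arm comparison uses neither site nor each parent's baseline score, so any test or interval computed from it as written would be too optimistic

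*Protocol article*

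**What the plan says.** The Design section states: "The pilot-testing stage (stage 2) is a 3-arm, cluster randomized pilot trial with parents accessing CAMHS". Under Stage 2 (Pilot-Testing Stage), "The 18 sites identified will be randomly assigned to either control or 1 of the 2 intervention groups", and "Participant-level randomization will not be conducted for this study". A parent's arm follows from the recruiting site: "Participants will be assigned to an intervention or control group based on the site from which they have been recruited". Up to 90 parents are to be invited, about 30 per arm.

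Table 1 places the CPS-P, PSDM-Q, STAI-AD, DCS and ESQ at both pretest and posttest. The PSSUQ is taken at posttest only.

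The sample-size paragraph gives a power figure "based on repeated measures" with three groups and two occasions: 30 parents in total, power 0.8, effect size 0.3. It mentions neither sites nor a design effect.

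Under Planned Analysis, Stage 2: Pilot-Testing Stage, the named comparison is that "between-group mean differences at the 2 time points (ie, baseline and follow-up) will be conducted". The same paragraph says the work is chiefly descriptive, "with some exploratory significance testing". It also says that standard deviations and ICCs of the shared decision-making measure will be estimated to plan the later trial.

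**The concern.** Parents at one site share clinicians, case mix and local practice, so their scores are likely to be correlated. When sites are the randomised units, the uncertainty of an arm difference depends on how much sites vary and how many there are. A test that counts 90 independent parents rejects too often, and an interval built the same way is too short.

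Separately, each parent's baseline score is collected but does not enter the follow-up comparison. That wastes precision. With few sites per arm, it also leaves chance differences at baseline uncorrected.

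Finally, the power figure and the analysis paragraph seem to describe different contrasts: change compared across arms in one, and arm differences at each occasion in the other. A reader cannot tell which analysis the effect size of 0.3 refers to.

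**Working it through.** **Inputs.** From the article: 3 arms, 18 planned sites, up to 90 parents, 2 occasions, and the stated N = 30, power 0.8 and effect size 0.3. The Results section adds that "to date, 11 CAMH sites have been recruited to take part in the study". Assumed here, because the article does not give them: alpha 0.05, effect size as Cohen's f, baseline to follow-up correlation r, and ICC 0.01 to 0.10.

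**1. The article's power figure.** For the group-by-time interaction on individuals, the noncentrality is λ = f²·N·m/(1 − r), where m is the number of occasions. With r = 0.5, λ = 0.09 × 30 × 2/0.5 = 10.8 on 2 and 27 df. Power is 0.8004, and N = 29 gives 0.784, so 30 is the smallest N that reaches 0.80. At N = 30, r = 0, 0.3 and 0.7 give 0.489, 0.648 and 0.957. At r = 0.5, the within-factor test gives 0.886 and the between-factor test 0.343. Of the variants tried, only the individual-level interaction with r = 0.5 and no design effect reproduces the figure.

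**2. Does it match the named comparison?** If arms do not differ at baseline, an interaction f of 0.3 corresponds to f = 0.6 at follow-up alone. Then λ = 0.36 × 30 = 10.8, and power is again 0.80. If 0.3 is instead the follow-up difference itself, λ = 0.09 × 30 = 2.7 and power is 0.27. So the meaning of 0.3 depends on which analysis is intended.

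**3. Effect of omitting site.** The design effect is DE = 1 + (n − 1)·ICC, where n is parents per site: 90/18 = 5, or 90/11 = 8.18. The true standard error is √DE times the parent-level one.

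For an F test on 2 and 87 df, P(F > x) = (1 + 2x/87)^(−87/2), so the 5% critical value is 3.10. Under clustering with no true effect, the between-arm mean square has expectation DE and the residual mean square c = (90 − 3·DE)/87. The true size is therefore about P(F > 3.10·c/DE). Example, 18 sites and ICC 0.10: DE = 1.40, c = 0.986, 3.10 × 0.986/1.40 = 2.18, and (1 + 4.37/87)^(−43.5) = 0.119.

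| Sites | ICC | DE | SE ratio | True size of nominal 5% test |
|---|---|---|---|---|
| 18 | 0.01 | 1.04 | 1.02 | 5.6% |
| 18 | 0.05 | 1.20 | 1.10 | 8.3% |
| 18 | 0.10 | 1.40 | 1.18 | 11.9% |
| 11 | 0.01 | 1.07 | 1.04 | 6.1% |
| 11 | 0.05 | 1.36 | 1.17 | 11.1% |
| 11 | 0.10 | 1.72 | 1.31 | 17.8% |

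A simulation with 60,000 runs per setting gave 5.6, 8.4 and 11.9% for 18 sites, and 6.1, 11.3 and 18.1% for 11 sites split 4/4/3. An analysis of variance on site means held 4.7 to 5.0% throughout.

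**4. Interval width.** For two arms of 30, in SD units, the parent-level 95% half-width is 2.002 × √(2/30) = 0.52. With 12 sites and 10 site-level df, it is 2.228 × √(2 × DE/30), which is 0.59, 0.63 and 0.68 at ICC 0.01, 0.05 and 0.10.

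**5. Effect of omitting baseline.** Adjustment multiplies residual variance by 1 − r²: 0.91, 0.75 and 0.51 at r = 0.3, 0.5 and 0.7. In the setting of step 1, with r = 0.5, λ rises from 10.8 to 10.8/0.75 = 14.4, and power rises from 0.80 to 0.90.

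**The case against.** The article condenses a fuller protocol that is not shown, and model terms are often left to that document or to an analysis plan. A reader might infer that the team plans a raw analysis and ignores clustering altogether. The text does not support that. It never says the comparison is unadjusted, and it does plan to estimate ICCs, although only for the shared decision-making measure and for use in the later trial.

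A reader might also infer that published confidence intervals will be too narrow, or that an overstated effect will drive the decision to proceed. Neither is documented. No interval is promised, and no efficacy test is said to decide progression. Omitting site also leaves the arm differences themselves unbiased.

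Two further points stand. Site randomisation was complete while parents were still being recruited, so describing baseline by arm can reveal differential recruitment. The fault would lie only in testing it, and the text does not say it will be tested. The two contrasts can also be read as compatible, since both use three groups and two occasions; this is ambiguity, not proven contradiction.

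The size of the problem rests on an unknown ICC and is negligible at 0.01 with 18 sites. Eleven is an interim count of sites, 90 is a maximum number of parents, and the 4/4/3 split is assumed.

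What survives is that tests are planned, one comparison is named, and the only inferential calculation shown treats parents as independent. Nothing stated makes those tests valid for a site-randomised design.

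**Conclusion.** The concern holds in limited form. As worded, the named comparison omits the randomised unit and the baseline score, and it does not clearly match the contrast behind the power figure. Any test or interval computed that way would be too optimistic because site is left out: a true size of about 6 to 12% with 18 sites of 5, or about 6 to 18% if 11 sites supply 90 parents, at assumed ICCs of 0.01 to 0.10. Leaving out baseline is a loss of efficiency, not an error, and its size depends on an unstated correlation. Severity is moderate, since Stage 2 is mainly descriptive and its tests are exploratory.

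**What to change.** In the Stage 2 planned analysis:

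- For the continuous scales measured at both times (PSDM-Q, STAI-AD, DCS, ESQ), state that any between-arm test or interval at follow-up adjusts for the baseline score and allows for site. This can be a mixed model with a random intercept for site and small-sample degrees of freedom, or a site-level analysis. The simulation above covers unadjusted site means only; the mixed model was not simulated.
- Present baseline scores by arm descriptively, without tests.
- Summarise the PSSUQ descriptively in app users, since it has no baseline and controls receive no app. Summarise the CPS-P by category, since it is a choice among five options.
- Reconcile the power statement with this analysis and with clustering: say which contrast the effect size of 0.3 refers to, and what correlation and ICC are assumed.

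The cost is revised wording, slightly more analysis work and wider intervals. No further data collection is needed.

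### The pilot's intraclass correlation is to feed the future RCT's sample size, but 18 sites of about 5 parents estimate it too imprecisely for that

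*Protocol article*

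**What the plan says.** The Design section describes stage 2 as a "3-arm, cluster randomized pilot trial with parents accessing CAMHS". Under Stage 2 (Pilot-Testing Stage), "The 18 sites identified will be randomly assigned to either control or 1 of the 2 intervention groups", and "Participant-level randomization will not be conducted for this study", so the site is the only randomized unit. On size, the same section says "Up to 90 parents, and their respective clinicians, will be invited to participate in this stage". The planned split is three groups of about 30 parents: one for each app version and one control.

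The Planned Analysis for stage 2 then gives the pilot estimates a specific use: "The standard deviations and intraclass correlation coefficients of the SDM measure will identify the parameters to enable planning for the subsequent trial". The next sentence is "The outcome of these analyses will be used to calculate the sample size for the future RCT". The sentence before these two announces between-group mean differences at baseline and follow-up. The section mentions no confidence interval, upper limit, range of ICC values, external ICC or minimum important difference.

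The Results section reports progress at the time of writing: "to date, 11 CAMH sites have been recruited to take part in the study".

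**The concern.** Asking a pilot for the SD and ICC is ordinary. The difficulty is that an ICC estimate depends mainly on the number of sites and on how many parents each contributes, and both are small here. The sample-size reasoning in the stage 2 section (10 to 30 per arm, and a power figure for 30 participants in total) does not address how precisely the ICC will be known.

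In a cluster trial the required number of participants is multiplied by the design effect, which rises with the ICC and with cluster size. A chance estimate near zero removes that multiplier, and a chance high estimate inflates it. Since the section gives informing the RCT design as part of its main aim, an unreliable planning input weakens one of the pilot's main products.

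**Working it through.** **The plan's own figure.** The article states power 0.8 for 30 participants in total at effect size 0.3, with 3 groups and 2 occasions. Assuming alpha 0.05 and a correlation of 0.5 between occasions, the noncentrality is 0.3² × 30 × 2 / (1 − 0.5) = 10.8, on 2 and 27 df, and the power is 0.80. The figure reproduces. It has no clustering term and says nothing about ICC precision.

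**Inputs from the documents.** 18 sites, 3 arms and up to 90 parents. Parents per site m = 90/18 = 5 at most on average, before dropout. Between-site df after arm = 18 − 3 = 15. Within-site df = 18 × 4 = 72.

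**Assumptions.** Equal site sizes, the one-way ANOVA estimator within arms, true ICC values of 0.01 to 0.10, and RCT cluster sizes M of 5 and 20. The documents give neither a true ICC nor an RCT cluster size.

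**Interval for an observed ICC of 0.05.**
- The matching variance ratio is F = (1 + 4 × 0.05)/(1 − 0.05) = 1.263.
- The 2.5% and 97.5% points of F on 15 and 72 df are 0.399 and 2.022.
- The limits for the ratio are 1.263/2.022 = 0.625 and 1.263/0.399 = 3.16.
- Converting with ICC = (F − 1)/(F + 4) gives −0.375/4.625 = −0.08 and 2.16/7.16 = 0.30.

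**Sampling distribution.** If the true ICC is 0.05, the estimate is zero or below when an F on 15 and 72 df falls below 1/1.263 = 0.792. That has probability 0.32. The central 95% of estimates run from about −0.11 to 0.24.

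| Sites × parents | ICC | 95% CI if this is observed | P(estimate ≤ 0) if this is true |
|---|---|---|---|
| 18 × 5 | 0.01 | −0.11 to 0.25 | 0.49 |
| 18 × 5 | 0.05 | −0.08 to 0.30 | 0.32 |
| 18 × 5 | 0.10 | −0.05 to 0.37 | 0.17 |
| 11 × 5 | 0.05 | −0.11 to 0.43 | 0.39 |
| 11 × 8 | 0.05 | −0.05 to 0.35 | 0.31 |

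The last two rows apply only if no more sites join the 11 already reported.

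**Effect on the RCT.** Design effect = 1 + (M − 1) × ICC. With a true ICC of 0.05 it is 1 + 4 × 0.05 = 1.20 at M = 5 and 1 + 19 × 0.05 = 1.95 at M = 20.
- Estimate taken as 0: planned over needed is 1/1.20 = 0.83 at M = 5 and 1/1.95 = 0.51 at M = 20. For an illustrative two-arm RCT with a standardized difference of 0.3 and power 0.80, the second case is 350 participants against 684, with actual power about 0.52.
- Estimate of 0.24: the design effect is 1 + 4 × 0.24 = 1.96 at M = 5 and 1 + 19 × 0.24 = 5.56 at M = 20. Planned over needed is 1.96/1.20 = 1.6 and 5.56/1.95 = 2.9.

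**SD and pilot difference.** Ignoring clustering, the pooled SD on 90 − 3 = 87 df is known to about −13%/+17%, which is usable if reported with its interval. A difference between two arms of 30, at ICC 0.05 and m = 5, has standard error √(2/30 × 1.20) = 0.283 SD. With t on 15 df (2.131), the 95% half-width is 0.60 SD.

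**The case against.** The strongest reply is that the article does not commit to plugging in point estimates, does not call the pilot the only source, and condenses a fuller protocol that is not shown. Confidence limits, ICC ranges and the target difference may be set out there or in the RCT's own protocol. That stands as a limit on the claim. It does not remove the point, because the article states a use for the pilot ICC, and the design it describes cannot support that use without a qualification.

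Two stronger readings are tempting. A reader might infer that the RCT will be about half the size needed. The documents do not support this. It requires a true ICC of about 0.05, some 20 parents per site and a team willing to plan a cluster trial with an ICC of 0. None of these is stated, nor is the RCT's unit of randomization. At the pilot's own 5 per site the same mistake leaves 83% of the needed size, and the error can equally oversize the trial.

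A reader might also infer that the observed pilot difference will be the RCT's target effect. The sentence on sample size follows directly after the one on SDs and ICCs, and the mean differences come one sentence earlier. The wording is open to that reading but does not say it. The 11 sites, likewise, are a count taken during recruitment and not the final design.

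**Conclusion.** The point holds in a limited form. The article makes the pilot ICC an input to the RCT sample size, and at most 18 sites of about 5 parents leave that ICC compatible with anything from no clustering to about 0.30 when 0.05 is observed. This imprecision follows from the stated design, given equal sites and full recruitment; fewer parents or fewer sites would generally widen it. The consequence for the RCT is conditional. At an assumed true ICC of 0.05, the planned size ranges from 83% (5 per site) or 51% (20 per site) of what is needed if the estimate is taken as 0, to 1.6 or 2.9 times what is needed if it is 0.24. The RCT cluster sizes are also assumptions. The SD is adequately estimated if its interval is given. The target difference needs only a clarifying sentence. This is a cheap improvement that should be made before the pilot data are used for planning; it is not a flaw in the pilot's feasibility aims.

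**What to change.** In the Planned Analysis for stage 2, replace the two sentences on planning parameters with wording that says:

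1. The ICC of the shared decision-making measure will be estimated within arms, reported with its 95% confidence interval, and used only as a consistency check.
2. The RCT sample size will be shown over a plausible ICC range, for example 0.01 to 0.10, informed by external data.
3. The SD will be reported with its confidence interval.
4. The RCT target difference will be a pre-specified important difference on the measure and not the difference observed in the pilot.

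The cost is a wording change and some work to find external ICC values. No additional participants or measurements are needed in the pilot. The drawback is that the RCT sample size becomes a range and may be larger than a single pilot-based figure.
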